### Data management

Data will be collected on paper case report forms (CRFs) designed specifically for the study. Data will be collected prospectively and kept confidential. The data will be collected in the local language using hard copy forms, with only the individual study identification number on each form. No subject names will appear in the forms.

For each participating woman, a study number (alpha-numeric, with check digit) will be assigned. A set of labels with each number is designed to be pasted on the CRFs of the mother and her children. Bar-coded labels (Brady, Milwaukee, Wisconsin) will be pasted on each of the blood samples. Names and other personal identifiers are recorded in the inclusion form header, which are stripped from the main body containing data. Each part is identified with a study label number. The inclusion form body will be sent to the local data center for data entry. With this system, it is ensured that personal identifiers will not be taken from the hospital and will be kept securely by the hospital coordinator.

Digital pictures (with date and time) of each CRF and the rapid tests used for screening will be taken in each country by the Field Research Coordinator and regularly sent encrypted to the Data Center by uploading the information to a cloud-based system (Dropbox) [41]. This system allows for a digital backup of all CRFs, as well as a parallel second data entry of 10% of the forms at the Data Center to detect systematic errors at data entry.

CRFs will also be entered on a daily basis in a secure web data management system called OpenClinica, which is open source software for clinical research studies using distributed data entry. This software has been adopted by the Department of Reproductive Health and Research of the World Health Organization as their data management systems, among other public research groups. The system was adapted (forms and rules) specifically for this study by the Clinical and Epidemiological Research Montevideo Unit (UNICEM, Montevideo, Uruguay), the study data center. The data forms, checks, and rules were designed by the study researchers in collaboration with the Data Center.

After the CRF has been entered into OpenClinica, it will be placed into a folder labeled with the participant’s unique subject ID. CRFs will be stored at the research unit’s data entry center in locked cabinets. Only the Country Data Manager has access to documents linking patient personal information to study ID code numbers.

The Country Data Manager in each country will send weekly reports to the Data Center regarding the screening, recruitment, consent, laboratory and follow-up processes of the study. The Data Center will prepare weekly reports about each site and send them to the Country Data Manager and to the Principal Investigator of the study.

### Sample size

We are planning to study 600 mothers with *T. cruzi* infection. The sample size will be achieved by recruiting 13,000 women in Mexico (estimated seroprevalence of 1% in Merida and 0.4% in Valladolid), 7,500 in Honduras (estimated seroprevalence of 4%), and 10,000 in Argentina (estimated seroprevalence of 2%). Based on our pilot study, we estimate that 20% of deliveries will be excluded because the age of the mother will be <18 or because consent is not obtained. In addition, we estimate that 5% of the women will be ineligible because they live outside of the follow-up area in Mexico (which includes the entire Yucatan Peninsula) and that 10% will live outside of the follow-up areas in Honduras and Argentina (which include only each hospital’s department or province).

We estimate that we will recruit 300 mothers with TcI infection and 300 mothers with Non-TcI infection. We will have more than 80% power to detect a difference of 1% transmission for TcI versus 5% for Non-TcI. We estimate that the loss to follow-up will be lower than 10%.

### Analysis plan

We will compute the rate of congenital transmission among seropositive mothers according to the exposure to TcI or Non-TcI with the corresponding confidence intervals and compare them using binomial exact tests. A seropositive mother will have at least one positive rapid test on cord blood and a positive ELISA on maternal blood. Cases with TcI/Non-TcI co-infection and with maternal HIV/AIDS will be analyzed separately, and transmission rates will be compared to the rest of the population.

In a second step, we will repeat the analysis after excluding infants with negative parasitological examinations and negative PCR on cord blood, and with a history of transfusion and/or organ transplant, and/or who are living in households exposed to the vector (presence of vectors and/or location in an area at risk of vector transmission). The resulting congenital transmission rate will be a more conservative estimate, which will be less likely to be biased by non-congenital routes of transmission. We will also stratify according to breastfeeding (yes/no), another potential route of neonatal transmission.

We will adjust the comparison of TcI/Non-TcI transmission rates for potential confounders:

– Maternal age at delivery (in five-year categories);

– Parity (primiparae/multiparae);

– Presence of vectors in the household (yes/no);

– Maternal parasitic DNA amount;

– Mode of delivery (C. section vs. vaginal); and

– Infected sibling (yes/no) (siblings previously treated for *T. cruzi* infection will be presumed as having been infected).

Mantel-Haenszel chi-square tests will be used for stratified analyses, which will take one categorical factor into account at a time. A logistic regression will be also performed and will include all potential confounders. Adjusted odds ratios (OR) and confidence intervals will be estimated.

We will describe birth outcomes (PROM, gestational age, birthweight, head circumference, length, and neonatal complications) of infected and uninfected infants by calculating proportions and confidence intervals for categorical variables (including preterm birth and low birthweight) and means and standard deviations for continuous ones. In a next step, we will stratify the analysis by DTU (TcI/Non-TcI). We will compare intrauterine growth restriction (IUGR) rates. A newborn will be classified as IUGR if its birthweight is below the tenth percentile of the sex-specific birthweight for gestational age curves proposed by Williams et al. [42] for single and multiple births. These growth curves are recommended by the WHO as reference patterns for international comparisons [43,44]. We will use the same reference for the three countries to allow for comparison among sites. In addition, we will also compute IUGR rates according to a more recent U.S. reference curve [45] for single live births to facilitate comparisons with the U.S. literature. We will also analyze birthweight data of infected and uninfected siblings by calculating proportions of low birthweight and “very small babies” and confidence intervals, mean birthweights, and standard deviations.

We will use STATA Version 8.0 [46] software for data analysis.

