## Background

Chagas’ disease, or American trypanosomiasis, is caused by the protozoan parasite *Trypanosoma cruzi*. It is a major cause of morbidity and mortality in the Americas, and an estimated 9 million persons are currently infected [1]. Of particular concern is the fact that mothers with Chagas’ disease can transmit *T. cruzi* to their fetuses [2].

Mother-to-child transmission of *T. cruzi* has all the characteristics required to be a public health priority, as it is relatively frequent, severe, identifiable, and treatable [3]. In reality, it is a neglected disease and a missed opportunity. Therefore, it is urgent to better understand the epidemiology of mother-to-child transmission and to develop effective prevention programs.

*T. cruzi* has been divided into Discrete Typing Units (DTUs): *T. cruzi* I (TcI) and *T. cruzi* Non-TcI (II-VI). In humans, TcI is predominant in Mexico and Central America, while Non-TcI is predominant in most of South America, including Argentina [4]. In recent studies from Argentina, the risk of congenital transmission has been estimated to vary between 2.6% and 7.9% [5-8]. By contrast, we know very little about the congenital transmission of TcI. It has been suggested that congenital transmission of *T. cruzi* is strain related [2,9], and there is an urgent need to know if TcI transmits differently than Non-TcI. Our primary hypothesis is that congenital transmission rates are different for TcI versus Non-TcI.

*T. cruzi* infected women living in regions where TcI is predominant could differ in terms of risk factors for transmitting *T. cruzi* to their offspring. Low maternal age, low parity, HIV/AIDS, exposure to vectors and high parasitic load have been reported as risk factors for congenital *T. cruzi* infection [9-14]. Family clustering has been observed in Argentina [15], suggesting that some mothers might be predisposed to transmit repeatedly.

There is limited information about the perinatal outcomes of infected infants in low endemicity areas. Congenital *T. cruzi* infection has been associated with premature rupture of the membranes and preterm births, in addition to neonatal complications [14]. Further studies are needed to document the impact of *T. cruzi* infection on perinatal outcomes.

The specific aims of this study are:

– 1. To determine the rate of congenital transmission of TcI compared to Non-TcI;

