### Entomological data

Entomological data will be obtained from two different sources to estimate vectorial exposure in the households from seropositive mothers. First, we will use vector distribution and house infestation data from the respective vector surveillance and control programs in Argentina and Honduras, which provide geocoded information and maps on the presence of vectors of different species at the village/locality level. For each household of a seropositive mother, we will thus determine if it is located in a village with or without known house infestation by triatomines using cumulated vector data from the past five years. For the Yucatan Peninsula, Mexico, in the absence of vector control programs, we will use published entomologic risk maps [22]. Based on these maps, households located in villages with low or absent risk will be classified as without house infestation, and households from villages with medium or high risk will be classified as with house infestation.

Second, we will use the community participation method, which was successfully piloted in and previously used in Argentina as well [23]. All of the households from seropositive mothers will be included, corresponding to an estimated 100 households in Mexico, 300 in Honduras, and 200 in Argentina. During the first household visit, information on Chagas’ disease and triatomines will be provided, including photographs and the display of dried specimens of the vector, to ensure that study participants will recognize the vector. Participants will then be instructed to collect any triatomines observed inside (domestic) or outside (peri-domestic) of their homes using a safe procedure and to place them into separate labeled plastic vials or bags. Any insects captured since the time of the initial visit will be gathered during the second visit at 10 months. Triatomine species will be identified by local entomologists from vector control programs in Argentina and Honduras and by entomologist researchers in Mexico, using established entomological keys [24,25].

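### The co-infection and HIV comparisons use a reference group that, as written, mixes TcI and Non-TcI mothers and is not adjusted for strain

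*Protocol article*

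**What the plan says.** All places are in the protocol article.

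- **Analysis plan, comparator:** "Cases with TcI/Non-TcI co-infection and with maternal HIV/AIDS will be analyzed separately, and transmission rates will be compared to the rest of the population". Neither strain nor country is named as a stratum for this comparison.
- **Analysis plan, adjustment:** the Mantel-Haenszel and logistic analyses are introduced with "We will adjust the comparison of TcI/Non-TcI transmission rates for potential confounders". The list that follows holds maternal age, parity, household vectors, parasitic DNA amount, mode of delivery and infected sibling. HIV and country are not on it.
- **Background:** "Our primary hypothesis is that congenital transmission rates are different for TcI versus Non-TcI".
- **Sample size:** "We will have more than 80% power to detect a difference of 1% transmission for TcI versus 5% for Non-TcI", with "We estimate that we will recruit 300 mothers with TcI infection and 300 mothers with Non-TcI infection".
- **Entomological data:** the households of seropositive mothers are put at a different mix, "corresponding to an estimated 100 households in Mexico, 300 in Honduras, and 200 in Argentina".
- **Variables:** when genotyping fails, strain is assigned by country. HIV status comes from whatever testing is routine in each country.

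**The concern.** Once co-infected and HIV-positive cases are set apart, the remainder is TcI and Non-TcI mothers together. If the primary hypothesis is true, that remainder has no single transmission rate. It has an average weighted by how many mothers each country recruited.

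The two comparisons suffer in different ways.

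- **HIV.** This is ordinary confounding. Strain group and HIV ascertainment are both tied to country, so HIV-positive mothers need not have the same strain mix as the rest. A group that transmits just like its HIV-negative neighbours could look like high or low transmitters, and a real effect could be hidden.
- **Co-infection.** Here strain is itself the exposure, so no same-strain reference exists. The difficulty is that the reference is a mixed rate. A co-infected rate of 3%, say, would be three times the TcI planning rate and below the Non-TcI one, and a single pooled comparison shows neither.

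The adjustment described in the same section does not reach either comparison.

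**Working it through.** **Inputs.** Planning rates of 1% (TcI) and 5% (Non-TcI), and 300/300 mothers, come from Sample size. The alternative mix of 400/200 comes from Entomological data: Mexico 100 + Honduras 300, against Argentina 200, taking one mother per household and strain by country. The size and strain mix of the HIV-positive group are not in the document and are assumed below.

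**1. The plan's own figure.** Two-sided alpha of 0.05 is assumed, since none is stated. The pooled proportion is 0.03.
- Null standard error: √(2 × 0.03 × 0.97 / 300) = 0.01393.
- Alternative standard error: √((0.01 × 0.99 + 0.05 × 0.95) / 300) = 0.01383.
- z = (0.04 − 1.96 × 0.01393) / 0.01383 = 0.918, which gives power of 82.1%.

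The claim of more than 80% is reproduced. (A Fisher exact test gives 79.8%.) The rates and sizes are therefore read as the plan meant them.

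**2. Reference rate of the mixed pool.**
- 300/300: (300 × 0.01 + 300 × 0.05) / 600 = 18/600 = 3.0%.
- 400/200: (400 × 0.01 + 200 × 0.05) / 600 = 14/600 = 2.3%.

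The two recruitment figures in the document alone move the reference from 3.0% to 2.3%.

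**3. HIV-positive group with no true effect.** Let a share f of m mothers be TcI. The group rate is f × 1% + (1 − f) × 5%. The rest is what remains of each strain group. With m = 20:

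| Share TcI | Group rate | Rest, 300/300 | Risk ratio | Rest, 400/200 | Risk ratio |
|---|---|---|---|---|---|
| 0% | 5.0% | 17.0/580 = 2.93% | 1.71 | 13.0/580 = 2.24% | 2.23 |
| 25% | 4.0% | 17.2/580 = 2.97% | 1.35 | 13.2/580 = 2.28% | 1.76 |
| 50% | 3.0% | 17.4/580 = 3.00% | 1.00 | 13.4/580 = 2.31% | 1.30 |
| 75% | 2.0% | 17.6/580 = 3.03% | 0.66 | 13.6/580 = 2.34% | 0.85 |
| 100% | 1.0% | 17.8/580 = 3.07% | 0.33 | 13.8/580 = 2.38% | 0.42 |

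With m = 60 the extremes are 0.31 and 1.80 at 300/300, and 0.40 and 2.45 at 400/200. At 400/200 the ratio is 1.0 when two thirds of the group are TcI. Within strain the ratio is 1.00 throughout (1% against 1%, 5% against 5%).

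**4. Masking.** Take 20 HIV-positive mothers, all TcI, with a true risk ratio of 3, at 300/300. They transmit at 3.0% against 3.07% in the rest, an apparent ratio of 0.98. Within TcI it would be 3.0.

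**5. Effect on a test.** No test is named for this comparison, so a two-sided Fisher test at 5% is assumed, enumerated exactly with no true HIV effect. False-positive rates against the mixed rest:

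| HIV-positive group | 300/300 | 400/200 |
|---|---|---|
| 5, all Non-TcI | 2.3% | 2.4% |
| 20, of whom 15 Non-TcI | 4.3% | 6.5% |
| 20, all Non-TcI | 7.5% | 10.5% |
| 30, all Non-TcI | 10.0% | 15.7% |
| 60, all Non-TcI | 16.4% | 26.2% |

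For the groups of 20, 30 and 60, the same test against their own strain rejects in 2.3% to 3.4% of cases. Steps 3 to 5 model HIV only. They do not describe co-infected mothers, who have no own-strain group.

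**The case against.** The strongest reply has four parts.

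- **Pooling is an inference.** The sentence before this one computes rates by strain with confidence intervals, so a reader will have the TcI and Non-TcI rates side by side. Showing the remainder by strain could be a detail that a condensed article leaves to the full plan. This stands in part: the separate rates will exist. But the article does name a comparator, and names it without strain. For birth outcomes the same section says outright that the analysis will be stratified by DTU.
- **Nothing inferential depends on it.** Neither HIV nor co-infection is an aim, a hypothesis or a powered comparison, and "compare them using binomial exact tests" is attached to the strain contrast. This stands, and it limits the weight of the point.
- **The large figures are extremes.** They need both a sizeable group and strong concentration in one region, and the documents show neither. This also stands. With five mothers the false-positive rate is about 2%, below nominal, and an even split of the group gives 2.0% to 4.4% for 20 or 30 mothers.
- **Both strains against one strain is a fair descriptive question.** This stands as description. It does not give the co-infected rate a stable reference.

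A reader might infer that the plan expects a fivefold difference. It does not. The 1% and 5% are a difference the study is sized to detect, and the hypothesis says only that the rates differ. The bias arises for any strain difference and shrinks with it.

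**Conclusion.** The point holds as a fault in a secondary comparison. As written, the HIV contrast is confounded by strain and country whenever HIV-positive mothers differ from the rest in strain mix, and no planned adjustment covers it. The co-infection contrast has a reference rate (3.0% or 2.3% on the plan's own figures) that moves with recruitment by country.

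On the planning rates, and for assumed groups of 20 to 60, a null HIV effect could appear as a risk ratio anywhere from about 0.3-0.4 to about 1.7-2.5. It would be 1.0 if the group were spread like the rest. This range assumes the 1% and 5% rates hold, and its ends assume full concentration in one strain.

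Two stronger readings are not supported. A reader might infer that the main result is compromised, but these cases are analysed apart and the TcI/Non-TcI contrast is untouched. A reader might also infer that a false-positive rate of up to 26% is to be expected. That figure rests on an assumed test, 60 assumed cases and an assumed split, none of which is in the document. The main harm is a misleading estimate. It is more than a wording matter, because the stated comparator can give the wrong answer.

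**What to change.** Replace the comparison with the rest of the population by two statements:

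- Co-infected cases will be reported against TcI-only and against Non-TcI-only mothers, separately.
- HIV-positive mothers will be compared with HIV-negative mothers within each DTU group, and the results combined by an exact stratified (Mantel-Haenszel) estimate where events allow.

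The pooled contrast can be kept, labelled as description only.

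**Cost.** It takes a sentence or two and a few more lines of output. No new data are needed, because strain group and HIV status are already recorded. The price is precision: reference groups are smaller and intervals wider. With transmission near 1% in TcI mothers and possibly few HIV-positive women, a stratum may have no events among them and contribute little or nothing. In that case the counts by stratum should be shown without a combined estimate.

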### Variables

The exposure to TcI will be defined by *T. cruzi* genotyping showing TcI on maternal blood and/or cord blood. In the absence of successful *T. cruzi* genotyping on maternal or cord blood, births occurring in Mexico or Honduras will be considered exposed to TcI.

The exposure to Non-TcI will be defined by *T. cruzi* genotyping showing Non-TcI on maternal blood and/or cord blood. In the absence of successful *T. cruzi* genotyping on maternal or cord blood, births occurring in Argentina will be considered exposed to Non-TcI.

The exposure to both TcI and Non-TcI (co-infection) will be defined by *T. cruzi* genotyping of both TcI and Non-TcI on maternal blood and/or on cord blood, or of TcI on maternal blood and Non-TcI on cord blood, or of Non-TcI on maternal blood and TcI on cord blood.

The primary outcome (Specific Aim 1) will be the congenital *T. cruzi* infection, which will be defined as the presence of one or more of the following criteria:

– Presence of parasites in cord blood (direct parasitological microscopic examination); and/or

– Presence of parasites in infant’s blood at 4–8 weeks (direct parasitological microscopic examination); and/or

– Persistence of *T. cruzi*-specific antibodies at 10 months, as measured by two tests.

A seropositive mother will have at least one positive rapid test on cord blood and a positive ELISA on maternal blood.

The mothers’ characteristics and exposure to vectors variables (Specific Aim 2) that will be collected include:

– Maternal age;

– Parity (including current birth);

– Infected sibling (yes/no) (siblings previously treated for *T. cruzi* infection will be presumed as having been infected);

– Maternal parasitic DNA amount;

– HIV serology (according to tests performed routinely in each country);

– Presence of vectors in the household (Infestation) (yes/no).

– Location in an area with risk of vectorial transmission (yes/no)

The birth outcomes (Specific Aim 3) to be measured are the following:

– Premature rupture of the membranes (PROM), defined as rupture of membranes before admission or before the onset of contractions, whatever the timing of the rupture; [14]

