A confirmatory ELISA will be performed for all 10-month follow-up tests that are positive or in question. The samples will be sent to Tulane University. Serologic analysis will be performed according to the manufacturer protocol using the FDA-cleared Hemagen Chagas Kit (Hemagen Diagnostics, Inc., Columbia, Maryland), a qualitative ELISA designed for the detection of circulating antibodies to *T. cruzi* in serum and plasma.

Congenital infection with *T. cruzi* is sought for by direct microscopic examination of blood buffy coat collected in six centrifuged microhematocrit heparinized tubes as previously described [2,14,38,39]. In those cases in which it is not possible to collect enough blood to fill 6 capillary tubes, collecting blood to fill at least one capillary tube will be considered acceptable. The detection limit of such parasitological detection was estimated to be 40 parasites/ml (p/ml) [38,39], which allowed the detection of more than 90% of the congenital cases in Bolivian endemic areas [40]. The number of positive microhematocrit tubes containing parasites, as well as the number of detected parasites per tube, allowed estimation of parasitemia as either low (≥ 40 p/ml - < 150 p/ml), medium (≥ 150 p/ml - ≤ 400 p/ml), or high (> 400 p/ml). Positive parasitological examinations will be filmed when possible. The films will be downloaded to the Chagas study webpage and shared between the study sites.

We will perform molecular tests to estimate the parasitic DNA amount (PCR followed by a qPCR in positive cases) and to identify the *T. cruzi* genotype (TcI and/or Non-TcI) on the blood of infected mothers. We will also perform PCR followed by genotyping on the umbilical cord blood samples. An international consensus has recognized direct parasitological examinations of cord or neonatal blood collected in capillary tubes, as well as serological investigations of infant blood at 10 months of age, as the best tools for the biological diagnosis of *T. cruzi* congenital infection, whereas PCR must still be standardized and validated for such use [2]. Thus, the research team is using blood parasitological examinations and late serology to identify infected newborns. PCR will not be used for diagnostic purposes, but it will aid in verifying the presence of parasitic DNA in samples before they are quantified via qPCR or before genotyping.

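### Co-infection can be assigned only where genotyping succeeds, yet the comparator takes in every ungenotyped mother, so the crude co-infection comparison carries an ascertainment bias

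*Protocol article*

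**What the plan says.** Four parts of the protocol article bear on this.

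- **Variables.** Co-infection rests on "genotyping of both TcI and Non-TcI on maternal blood and/or on cord blood", or on one type in the mother and the other in the cord. There is no fallback for co-infection. For single strains there is one: without a successful genotype, "births occurring in Mexico or Honduras will be considered exposed to TcI", and likewise "genotyping on maternal or cord blood, births occurring in Argentina will be considered exposed to Non-TcI".
- **Blood samples and laboratory evaluations.** PCR is not used for diagnosis; "it will aid in verifying the presence of parasitic DNA in samples before they are quantified via qPCR or before genotyping". Quantification by qPCR follows only in PCR-positive cases.
- **Background.** "Low maternal age, low parity, HIV/AIDS, exposure to vectors and high parasitic load have been reported as risk factors" for congenital infection.
- **Analysis plan.** Co-infected cases are analysed separately, "and transmission rates will be compared to the rest of the population". Nothing limits that comparator to genotyped mothers. Maternal parasitic DNA amount is on the list of adjustment variables, but that list is attached to the TcI versus Non-TcI comparison.

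The quoted Analysis plan sentence also covers mothers with HIV/AIDS. That comparison does not depend on genotyping and is not at issue here.

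**The concern.** The two sides of the comparison are ascertained differently. A mother enters the co-infected group only if a specimen held enough parasite DNA to be typed. A mother with a negative PCR or failed typing can only enter the comparator, whatever strains she carries. If typed mothers have higher loads, and higher load goes with more transmission, the co-infected group will show a higher transmission rate even if carrying two strains makes no difference.

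There is a second route. Cord-blood genotypes also count. Parasite DNA in cord blood is likelier when the infant is infected, so the chance of finding a second type depends partly on the outcome. The article's own second-step analysis treats a negative cord PCR, together with negative parasitology, as a mark of possibly non-congenital infection, which fits that reading.

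At stake is whether a higher rate in co-infected cases could be read as an effect of mixed infection. The primary TcI versus Non-TcI comparison is not the subject of this point.

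**Working it through.** **The plan's own figures.** The article gives no figure for the co-infection comparison. Its planning figures are for the primary comparison: 300 and 300 mothers, 1% versus 5%, power above 80%. That power reproduces at 82.1% (normal approximation, two-sided 5% assumed). It is context only; the planning rates are used in step 4.

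**1. Inputs.** From the documents: the assignment rules, the DNA requirement, the direction of the load effect, and 600 infected mothers. Assumed, because the documents do not give them:

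- g, the share of mothers genotyped
- k = r1/r0, transmission in genotyped mothers divided by transmission in ungenotyped mothers
- c = 5%, the share of genotyped mothers found co-infected

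**2. Model with no true co-infection effect.** All genotyped mothers transmit at r1 and all others at r0. The co-infected rate is r1. The comparator rate is [g(1−c)r1 + (1−g)r0] / (1−gc). Dividing,

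spurious ratio = k(1−gc) / [g(1−c)k + 1−g].

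Worked case, g = 50%, k = 4, overall transmission 3%:

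- r0 = 0.03 / (0.5×4 + 0.5) = 1.2%, and r1 = 4.8%
- comparator = (0.475×4.8% + 0.5×1.2%) / 0.975 = 2.95%
- ratio = 4.8 / 2.95 = 1.62

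| g | k = 2 | k = 4 | k = 8 |
|---|---|---|---|
| 30% | 1.55 | 2.14 | 2.64 |
| 50% | 1.34 | 1.62 | 1.81 |
| 70% | 1.18 | 1.30 | 1.37 |

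The ratios do not depend on the overall transmission rate.

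**3. Near the limits.**

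- g = 95%, k = 4: 4×0.9525 / (0.9025×4 + 0.05) = 3.81 / 3.66 = 1.04
- g = 50%, k = 1.2: 1.2×0.975 / (0.475×1.2 + 0.5) = 1.17 / 1.07 = 1.09
- k = 1: exactly 1.00 for any g

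**4. Country mix.** The comparison as written pools countries. At the planning rates the pooled average is (300×1% + 300×5%) / 600 = 3%. With no load effect, co-infected mothers all transmitting at the TcI rate would give about 1/3 = 0.33. All transmitting at the Non-TcI rate would give about 5/3 = 1.67. Multiplied by the 1.62 above, these become roughly 0.54 and 2.7. This ignores the small shift from removing co-infected mothers from one stratum.

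**5. Expected events.** Co-infected mothers number 600×g×c: 9 at g = 30%, 15 at 50%, 21 at 70%. In the worked case the expected number of infected infants among them is 15×4.8% = 0.72.

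**6. Comparator limited to genotyped single-type mothers.** In this model the ratio is r1/r1 = 1.00, but only because the model gives all genotyped mothers the same load.

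**The case against.** The strongest opposing case has five parts.

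- **Importance.** Co-infection is in none of the three specific aims and has no hypothesis or power statement. With perhaps 9 to 21 co-infected mothers and about one infected infant or fewer, sampling error would swamp a distortion of this size. This stands as a limit on importance. It does not remove the bias, because the article states the comparison and fixes its comparator.
- **Net direction.** A reader might infer that the planned comparison must come out in favour of co-infection raising transmission. The documents do not support that. Only the load-related part has a known sign; country mix at the planning rates can reverse the pooled ratio (step 4).
- **Cord blood.** A reader might infer that co-infection can be found only in mothers whose own blood holds enough DNA. The Variables section also accepts cord blood, so that is too narrow. A correction for maternal load alone would therefore not be enough.
- **Size.** Genotyping success and load effect are not given, and the article does not equate being typable with having a high load. This stands: the range is conditional, and it shrinks to nearly 1 near the limits.
- **Condensed article.** Details of a sparse secondary analysis may sit in the full protocol or SAP, and maternal DNA amount is collected. But the assignment rule and the comparator are both stated here, and it is their combination that gives the bias. Nor could the listed adjustment simply be extended: mothers with a negative PCR have no qPCR amount.

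**Conclusion.** The point holds as an ascertainment bias in a secondary comparison. Co-infected cases are selected on successful genotyping and the comparator is not, while the article itself links genotyping to detectable DNA and high load to transmission. Taken alone, this raises the co-infection ratio. The rise is about 1.2 to 2.6 for g = 30% to 70%, k = 2 to 8 and c = 5%, all assumed, and close to 1 when g nears 100% or k nears 1. Outcome-dependent detection through cord blood adds a second bias, whose size cannot be computed from the documents. Country mix adds a third influence of either sign, so the net direction of the pooled result is not certain.

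A reader might also infer that limiting the comparator to genotyped mothers restores an unbiased ratio of 1.0. That is true in the model by construction only. Detecting two types may need more DNA than detecting one, and the documents do not say otherwise. The change is worth making because it is cheap, not because any primary conclusion depends on it.

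**What to change.** For the co-infection comparison only, amend the Analysis plan as follows:

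- Define both groups by the same rule, genotyping of maternal blood alone.
- Compare mothers showing both types with mothers whose genotyping succeeded and showed a single type, stratified by country where numbers allow.
- Show maternal parasitic DNA amount in both groups, so that any remaining load difference is visible.
- Report ungenotyped mothers and their transmission rate separately, outside this comparison.
- Label the result exploratory.

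This needs a few lines of text and no new samples or tests, and it leaves the primary TcI versus Non-TcI analysis as it is. The cost is a smaller comparator and the loss of co-infections seen only through cord blood, in a comparison that will have few events in any case. Within a country there may be too few to estimate a ratio, in which case counts should be given instead.
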